### Secondary Efficacy Endpoints

6.2

The key secondary efficacy endpoints are time from randomization to the first occurrence of the composite of the following events:
84‐week change in Quality‐of‐life assessment by the EQ‐5D and ICECAP‐A.12‐, 56‐ and 84‐week adherence to home BP measurements.12‐, 56‐ and 84‐week prescription and adherence to anti‐hypertensives, lipid‐lowering, and anti‐hyperglycemic therapies.

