**Methods:**

This is an open‐label randomized and decentralized clinical trial describing the design and methodology of the TAMIS program, which will assess its impact on community‐dwelling diabetic subjects with uncontrolled HBA1c and uncontrolled LDL‐C and/or blood pressure. Individuals will be randomized to usual care or remote care and followed for 84 weeks. Remote monitoring offers a practical response to the limited capacity of LMIC health systems to ensure sustained follow‐up and continuity of care for chronic conditions. The primary endpoint is a win‐ratio of hierarchical events, including all‐cause deaths and the frequency of all‐cause hospitalizations. The secondary endpoints include control of HbA1c, LDL‐C and blood pressure according to clinical guidelines, as well as patient‐reported outcomes and clinical parameters, including blood pressure, glycemic control, and LDL cholesterol levels. Subgroup analyses will explore the impact of demographics and clinical characteristics on treatment outcomes. Overall, the study aims to improve health care delivery, enhance patient education, and foster collaboration between patients and health care providers to mitigate the growing burden of cardiovascular diseases in LMICs.

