### Statistical Methods

9.4

All continuous variables will be presented as median and interquartile range (IQR), while categorical variables will be reported as absolute (n) and relative frequency (%).

Descriptive statistics (mean ± standard deviation, median and IQRs) will be generated for each treatment group to summarize demographic and baseline characteristics. Between‐groups comparisons will be conducted within the Intention‐to‐Treat (ITT) population to ensure that the randomization process successfully achieved balance between groups. Differences in baseline characteristics between treatment groups will be tested using a chi‐square test for categorical variables and a two‐tailed *t*‐test with treatment as a factor for continuous variables. These preliminary analyses will serve as an initial assessment of the adequacy of randomization.

The primary endpoint analysis will be performed using a win‐ratio test, which combines time to all‐cause death and the frequency of nonfatal hospitalizations. The win ratio test will follow the original methodology described by Pocock et al. [16]. Beyond hierarchical endpoint evaluation, this approach allows for the integration of multiple endpoint types. Treatment differences will be tested at an alpha level of 0.05, with a sequential procedure for controlling type 1 error. Additional covariate adjustments for time‐sensitive analyses will be performed using a Cox proportional hazards model, incorporating the randomization stratification factor. The HR for treatment groups will be reported along with the 95% confidence interval (CI).

The secondary endpoint analysis will be performed using Kaplan‐Meier survival curves, evaluating time‐to‐event data for each secondary efficacy endpoint. The log‐rank test used for the primary endpoint analysis will also be applied to secondary endpoints. Treatment differences will be tested at an alpha level of 0.05, employing a sequential procedure for type 1 error correction. Covariate adjustments for time‐dependent analyses will again be performed using the Cox proportional hazards model, with the HR and 95% CI reported.

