For non–time‐to‐event secondary endpoints, including changes in metabolic and clinical parameters (blood pressure, HbA1c, LDL‐C) and patient‐reported outcomes, analyses will be performed using paired t‐tests and analysis of covariance (ANCOVA) models, incorporating baseline values as covariates. Treatment differences will be evaluated at a two‐sided alpha level of 0.05, applying the same hierarchical procedure used for time‐to‐event endpoints to control type I error. All analyses will follow the ITT principle, and sensitivity analyses will be conducted to assess the impact of missing data.

For the tertiary endpoint analysis, the study will evaluate changes in the MeTaRiSc from baseline to Week 84. Each participant will receive a score of 1 for each parameter above the target; the total score will then be divided by three, producing a weighted mean ranging from 0 to 1. A paired t‐test will compare the two treatment groups. Treatment differences will be tested at an alpha level of 0.025, using a sequential type 1 error correction procedure. Covariate adjustments will be made using a *t*‐test, incorporating the randomization stratification factor. The mean values for each treatment group (intervention vs. control) will be reported with the corresponding 95% CI.

All subgroup analyses will involve log‐rank tests and the hazard ratios (with 95% CIs) for primary and secondary efficacy endpoints. The predefined subgroups include sex, age (< 65 vs. ≥ 65 years), prior cardiovascular disease, presence of cardiovascular risk factors (diabetes, hypertension, chronic kidney disease), smoking history (active vs. significant past smoking), obesity/metabolic syndrome, and prior statin use.

The present study was designed in accordance with the NIH‐FDA Clinical Trial Protocol Template. A structured protocol and a Statistical Analysis Plan (SAP) were developed prior to participant enrollment, specifying the analytic approach for all predefined endpoints, including sensitivity and subgroup analyses.

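### Section 6.2 defines the key secondary endpoints as a time-to-first-event composite but lists no events, and the set of secondary endpoints differs between the abstract, 6.2 and 9.4

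*Protocol article*

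**What the plan says.** Section 6.2 (Secondary Efficacy Endpoints) begins: "The key secondary efficacy endpoints are time from randomization to the first occurrence of the composite of the following events". Three items follow:

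- "84‐week change in Quality‐of‐life assessment by the EQ‐5D and ICECAP‐A"
- "84‐week adherence to home BP measurements", also at weeks 12 and 56
- "84‐week prescription and adherence to anti‐hypertensives, lipid‐lowering, and anti‐hyperglycemic therapies", also at weeks 12 and 56

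The Methods paragraph of the abstract gives a different set: "The secondary endpoints include control of HbA1c, LDL‐C and blood pressure according to clinical guidelines", together with patient-reported outcomes and clinical parameters.

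Section 9.4 (Statistical Methods) describes the secondary analysis twice. First: "The secondary endpoint analysis will be performed using Kaplan‐Meier survival curves, evaluating time‐to‐event data for each secondary efficacy endpoint", with log-rank tests and a Cox model. Next, it addresses secondary endpoints that are not time-to-event, "including changes in metabolic and clinical parameters (blood pressure, HbA1c, LDL‐C) and patient‐reported outcomes". These are to be analysed with paired t-tests and ANCOVA adjusted for baseline, at two-sided 0.05, under the same hierarchical procedure as the time-to-event endpoints. Section 9.4 also plans log-rank tests and hazard ratios for all subgroup analyses of primary and secondary endpoints.

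Section 6.3 makes MeTaRiSc the tertiary endpoint. It scores home systolic pressure, LDL-C and HbA1c against targets.

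**The concern.** A time-to-first-event composite needs components that occur at a point in time. A change in EQ-5D between baseline and week 84, or an adherence level at week 12, is a value read at a set visit. Without a threshold that turns it into an event, it has no occurrence time and cannot be a first occurrence of anything. The direction is unclear too: adherence is a good outcome, so a hazard ratio for a composite that includes it has no plain meaning.

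The second difficulty is membership. The programme aims at risk factor control, and eligibility requires HbA1c above target plus uncontrolled blood pressure and/or LDL-C. The abstract accordingly names control of these three factors as secondary, but the only section that lists secondary endpoints leaves them out.

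What is at stake is pre-specification. A sequential procedure protects the type I error only if the endpoints and their order are settled in advance. In an open-label trial with several incompatible lists, a later report could present control, change or some composite as the planned key secondary result.

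**Working it through.** The plan gives no figure to reproduce and no arithmetic decides the point. The check sets the statements side by side.

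| Outcome | Abstract | Section 6.2 | Section 9.4, survival paragraph | Section 9.4, non-time-to-event paragraph |
|---|---|---|---|---|
| Guideline control of HbA1c, LDL-C, BP | Secondary | Not listed | Covered only through the word each | Not named |
| Levels or changes in BP, HbA1c, LDL-C | Secondary | Not listed | As above | Named; ANCOVA, in the hierarchy |
| EQ-5D and ICECAP-A | Secondary (as patient-reported outcomes) | Listed as part of the composite | Kaplan-Meier, log-rank, Cox | Named as patient-reported outcomes; ANCOVA, in the hierarchy |
| Adherence to home BP measurement | Not named | Listed as part of the composite | Kaplan-Meier, log-rank, Cox | Not named |
| Prescription of and adherence to drugs | Not named | Listed as part of the composite | Kaplan-Meier, log-rank, Cox | Not named |

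**Step 1: is any listed item an event?** The first is a change score. The second and third are states at weeks 12, 56 and 84. Section 2.1 supplies an 80% rule for adherence, but it classifies a participant over follow-up and does not date an event. Count: 0 of 3.

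**Step 2: are the abstract's control endpoints in 6.2?** HbA1c, LDL-C and blood pressure control: 0 of 3. In the Outcomes section they contribute to efficacy only as components of the tertiary score in 6.3.

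**Step 3: does 9.4 agree with itself and with 6.2?** Quality of life is a component of a time-to-event composite in 6.2, falls under "evaluating time‐to‐event data for each secondary efficacy endpoint" in one paragraph of 9.4, and is non-time-to-event in the next. These three statements cannot all hold. Of the three items in 6.2, the non-time-to-event paragraph expressly names only this one, so the two adherence items are left with survival methods that do not fit them.

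**Step 4: are week-84 laboratory values secured in both arms?** Section 2.1 lists blood samples at baseline and weeks 12, 24, 36, 56 and 84, without separating the arms. Section 5 gives the control arm laboratory tests every 24 weeks. Counted from baseline, that means weeks 24, 48 and 72, then 96. Only week 24 is on both schedules, and 84/24 = 3.5, so week 84 is not on the control-arm cycle. The two sections must be reconciled.

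**The case against.** The strongest reply is that 9.4 already contains much of the repair. It separates non-time-to-event secondary endpoints, gives them ANCOVA and places them in the hierarchy. That stands for quality of life and for changes in blood pressure, HbA1c and LDL-C. It does not mend the definition in 6.2, does not withdraw the survival analysis of every secondary endpoint, and speaks of change where the abstract speaks of control.

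A reader might infer that the risk factor outcomes are tested outside the sequential procedure, and might attach a family-wise error of 1 − 0.95³ = 0.143 for three independent tests at 0.05. The document does not support this. Section 9.4 puts the changes inside the hierarchy, and its list is introduced as non-exhaustive, so even the control endpoints are not shown to be outside. The supportable complaint is that membership and order are inconsistent.

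A reader might also conclude that no secondary analysis can be run. That is true only of the composite in 6.2.

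It can be said that 6.2 covers only the key secondary endpoints, so that a wider list may exist. No wider list is given, and the subset reading does not make change scores into events. Nor are the control parameters wholly absent from the Outcomes section, since 6.3 uses them. The fault there is rank: secondary in the abstract, tertiary score in 6.3.

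Finally, model detail may properly sit in the analysis plan, which is not shown. That is a fair limit on omissions, but these are conflicting statements within the article about what the endpoints are.

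**Conclusion.** The point holds as a contradiction in the text. The composite in 6.2 is undefined because none of its three items is an event. None of the three control endpoints in the abstract is in 6.2. The abstract, 6.2 and the two secondary-analysis paragraphs of 9.4 do not describe the same set of endpoints for the sequential procedure.

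No numerical inflation of type I error can be derived from the document, and none is claimed. The primary endpoint, randomization and sample size are untouched. The conclusion rests on reading 6.2 as the only list of secondary endpoints in the Outcomes section, and on the list as printed being complete; no gap or redaction is marked there.

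**What to change.** 1. In 6.2, delete the time-to-first-event lead-in and list separate secondary endpoints: control of HbA1c, LDL-C and blood pressure from the abstract; changes in blood pressure, HbA1c and LDL-C from 9.4; change in EQ-5D and ICECAP-A; and the adherence and prescription measures. State the assessment week of each, and the target that defines each control endpoint.
2. Fix the order of these endpoints in the hierarchy, and make the abstract, 6.2 and 9.4 agree on it.
3. In 9.4, keep the planned ANCOVA for continuous changes. For control and adherence proportions, use a binary-outcome model adjusted for baseline, where a baseline value exists, and for the stratification factors.
4. Restrict Kaplan-Meier, log-rank and Cox, including in the subgroup analyses, to true time-to-event outcomes such as death.
5. Reconcile 2.1 and 5 on control-arm laboratory timing so that week-84 values are available in both arms.

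Items 1 to 4 cost only wording in the protocol and analysis plan. Item 5 may also be wording if the Schedule of Activities, which is not shown, already places a week-84 sample in the control arm. If it does not, a visit has to be added. Whether control participants measure blood pressure at home should be confirmed at the same time, because 5.2 describes the monitors among the intervention procedures.

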To bridge these gaps, we have developed the TriAl on the remote Management and control of blood pressure, glycemia, and lipids in a diverse community‐baSed population—Artificial Intelligence platform (TAMIS‐IA), a structured and remotely delivered chronic disease management program. TAMIS‐IA integrates guideline‐based, algorithm‐driven clinical workflows for hypertension, diabetes, and dyslipidemia management. For hypertension, patients perform structured home blood pressure monitoring during 6 consecutive days, with automated calculation of aggregated blood pressure averages guiding predefined titration pathways. For diabetes, remote follow‐up includes structured lifestyle assessment, pharmacologic adjustment according to algorithms based on the American Diabetes Association (ADA) guidelines, and scheduled laboratory reassessments. LDL‐C management follows a stratified risk‐based protocol incorporating laboratory safety parameters and contraindication screening prior to therapeutic escalation. All therapeutic recommendations generated by the system are reviewed and approved by supervising physicians before implementation.

This study will evaluate the clinical impact of TAMIS‐IA on major clinical outcomes, providing valuable evidence on the effectiveness of remote chronic disease management models in LMICs. By leveraging technology‐driven interventions, this trial aims to establish a scalable, cost‐effective, and sustainable strategy for improving long‐term cardiovascular risk management in underserved populations.

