**Figure 1 jep70456-fig-0001:**
[figure not shown]
Overview of patient flow and study design.

Participant selection and randomization involve confirming interest, explaining the study details, and assessing eligibility. Baseline demographic data, medical history, and health status will be collected before randomization. During follow‐up visits, the study team will: (i) measure blood pressure and glycemic levels; (ii) administer the study protocol; (iii) monitor symptoms and adverse events, and (iv) evaluate treatment adherence.

Adherence will be defined as the completion of at least 80% of scheduled home measurements and the use of at least 80% of prescribed medication doses during follow‐up. Data will be obtained through the TAMIS‐IA platform and scheduled study visits. Participants meeting both criteria will be classified as adherent in secondary analyses. Low adherence will be addressed through sensitivity analyses.

At baseline and weeks 12, 24, 36, 56, and 84, blood samples will be collected, laboratory tests performed, and study endpoints assessed. At week 84, similar follow‐up procedures will take place, with additional endpoint evaluations and final blood sample collection. In addition to these scheduled in‐person laboratory assessments, follow‐up incorporates structured remote contacts and digital data capture. Participants are not required to attend in‐person visits for each follow‐up interaction. In the intervention arm, counseling and medication titration discussions are conducted remotely by trained monitors under physician supervision. Throughout the study, all data will be systematically documented and entered into a secure database. Additionally, quality of life will be assessed using the European Quality of Life 5 Dimensions (EQ‐5D) and the ICEpop Capability Measure for Adults (ICECAP‐A) at multiple time points. The description of the study procedures and measurements is provided in Supporting Information Material 1: Schedule of Activities and illustrated in Figure 2.

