## Interventions

5

Participants in the control arm will receive treatment at the discretion of their physician, without interference from the study personnel, and they will be followed up through app interactions, phone calls, and lab exams every 24 weeks.

Both study arms are recruited and followed within the same BHU of the Brazilian Primary Health Care Network, ensuring comparable clinical settings and multidisciplinary staff. Usual care in these units is provided by PCPs and nurses and is defined as routine management typically involving in‐person consultations every 3–6 months according to clinical need, with medication adjustments and laboratory testing performed at the physician's discretion, and no structured digital follow‐up. In the control arm, no standardized algorithms or automated decision‐support tools are used, and there are no scheduled tele‐touchpoints beyond those required for data collection. All usual‐care contacts and visit frequencies will be documented to allow comparison of exposure intensity between study arms. To minimize contamination between study arms, the structured remote workflow is delivered exclusively by the trained study monitors assigned to the intervention arm. Control participants do not have access to TAMIS‐IA clinical decision support, automated titration protocols, or structured telemonitoring beyond protocol‐required data collection. Usual care providers remain independent from the intervention workflow, and no algorithm‐driven recommendations are integrated into routine care.

Participants in the active intervention arm will receive treatment based on standardized clinical guidelines, with instructions provided remotely by study monitors under physician supervision. The study monitors are health care professionals and research fellows with clinical backgrounds, specifically trained to conduct structured telephone follow‐ups, data collection, and patient education activities. The intervention is supported by TAMIS‐IA, a web‐based digital health platform that enables remote management, patient monitoring, and clinical decision support. All medication adjustments or new prescriptions generated through the digital platform are reviewed and formally approved by physicians before implementation to ensure clinical safety and protocol compliance. Further technical and operational details of the platform are provided in Supporting Information S1: Material 2.

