### Blood Pressure Management

5.2

A SAH treatment algorithm was developed based on the 2025 Brazilian Hypertension Guideline [11]. Figure 3 illustrates the clinical workflow for SAH management, including the initiation and titration of pharmacological treatment. Upon enrollment, patients will measure their BP at home for six consecutive days, following a standardized protocol: twice in the morning and twice in the evening, always before taking antihypertensive medications. Patients will receive home BP monitors, equipped with technology that enables real‐time transmission of BP readings to the EHR via Bluetooth.

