### Tertiary Efficacy Endpoint

6.3

The change in the ‘metabolic target risk score’ (MeTaRiSc) from baseline to week 84. Each individual will be assigned the value 1 for each parameter above the targets, and the sum of the 3 parameters will be divided by 3. The MeTaRiSc is this weighted mean that varies from 0 to 1.
i.+1 if more than 10% of home SBP measurements ≥ 130 mmHg.ii.+1 point if LDL cholesterol levels are above targets defined by the 2013 ACC/AHA cholesterol guidelines;iii.+1 point if glycated hemoglobin (HbA1c) levels ≥ 7.0%.

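### Adherence to home blood pressure measurement is tested between arms as a key secondary efficacy endpoint, although structured home monitoring is a component of the intervention

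*Protocol article*

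**What the plan says.** **Status of the endpoint.** Section 6.2 opens with "The key secondary efficacy endpoints are time from randomization to the first occurrence of the composite of the following events" and then lists, among other items, "week adherence to home BP measurements" at weeks 12, 56 and 84. Section 9.4 provides Kaplan-Meier and log-rank analysis for time-to-event secondary endpoints and t-tests and ANCOVA for the others. Treatment differences are judged at alpha 0.05 in both cases, within a sequential or hierarchical procedure. Nothing confines the adherence item to one arm or calls it a process measure.

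**Who does home monitoring.** The Introduction describes the TAMIS-IA programme with the words "For hypertension, patients perform structured home blood pressure monitoring during 6 consecutive days". Section 5.2, within the Interventions section, says "Patients will receive home BP monitors" and sets four readings a day for six days, with another cycle after each titration. In Section 5, usual care has "no structured digital follow‐up", and controls have no structured telemonitoring apart from what the protocol's data collection needs. Their follow-up consists of app contacts, telephone calls and laboratory tests.

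**Where else home readings are used.** Section 2.1 defines an adherent participant partly by "completion of at least 80% of scheduled home measurements". Section 6.3 gives one MeTaRiSc point when "more than 10% of home SBP measurements" reach the systolic threshold, and Section 9.4 compares that score between arms.

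**The concern.** An efficacy endpoint should measure something that the intervention might or might not change, and it should be observed in the same way in both arms. Taking home readings in structured cycles is something the programme itself supplies, schedules and follows up by telephone. Comparing its uptake with an arm that is not given that structure measures how well the programme was delivered.

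Two things are at stake. The first is interpretation: a significant result could be reported as a positive key secondary efficacy finding although it says little about patient benefit. The second is measurement: the adherence definition needs a count of scheduled readings, and the only schedule that the article describes is the titration workflow of the intervention arm. The same question of comparability reaches the adherence classification and the first MeTaRiSc item, because both draw on home readings.

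**Working it through.** There is no stated figure to reproduce. The check is a comparison of sections, followed by an illustration.

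1. **Is the item tested between arms?** Yes. It is listed as secondary efficacy (Section 6.2), and Section 9.4 tests secondary endpoints for treatment differences.
2. **Is home monitoring part of the intervention?** Yes. The Introduction names it as part of TAMIS-IA. Section 5.2 links each further cycle to an algorithm-driven titration, and the control arm has no such algorithm (Section 5).
3. **Do controls have a comparable schedule?** The article gives none. Section 5 leaves room for readings needed for data collection, and MeTaRiSc needs home systolic readings at baseline and week 84, so some common readings may exist. Beyond those, only the intervention arm has scheduled readings that the article describes.
4. **Is the adherence count the same quantity in both arms?** It can be for common data-collection readings. It cannot be for titration-cycle readings, which have no counterpart in controls.

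**Illustration.** The article gives no adherence rates, so all proportions here are assumptions. Section 7 gives 419 per arm and 5% attrition: 419 × 0.95 = 398 per arm. For a two-sided test at 0.05,

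power ≈ Φ[(|p₁ − p₀| − 1.96·SE₀) / SE₁],

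with SE₀ = √(2p̄(1 − p̄)/n), SE₁ = √((p₀(1 − p₀) + p₁(1 − p₁))/n), and p̄ the mean of p₀ and p₁.

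- Control 40%, intervention 50%: SE₀ = 0.0353, SE₁ = 0.0351, so Φ[(0.10 − 0.0691)/0.0351] = Φ(0.88) = 81%.
- Control 20%, intervention 50%: SE₀ = 0.0338, SE₁ = 0.0321, so Φ[(0.30 − 0.0663)/0.0321] = Φ(7.3), about 100%.
- Control 0% to 20% against intervention 50% to 80%: about 100% at every combination computed.

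So if controls have much less structured monitoring, a significant difference is practically assured. If the arms are closer, it is likely but not certain.

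**The case against.** The best defence is that the article never says controls take no home readings. Section 5 excludes telemonitoring only beyond data-collection needs, Section 2.1 defines adherence for participants generally, Section 5.2 names no arm when it speaks of supplying monitors, MeTaRiSc needs home readings in both arms, and the Schedule of Activities is a supplement that is not shown. This stands. A reader might infer that controls have no scheduled readings at all and hence no denominator, but the documents do not support that. What remains is that the titration-linked cycles, and the monitor calls that act on them, belong to one arm only. Uptake of measuring is still a fidelity measure even if some readings are shared.

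A reader might also build a large ratio of scheduled readings within the intervention arm: 588 days / 13 days per cycle ≈ 45 cycles × 24 readings ≈ 1,085 if never controlled, against 4 × 24 = 96 if controlled at once, about 11-fold. This does not hold. Section 5.2 calls the cycle biweekly (42 cycles, 1,008 readings) and ties each repeat to a titration. It also refers patients who are still elevated on three agents to a specialist, so continuous cycling for 84 weeks does not fit the pathway. The lower figure assumes one cycle per six-month follow-up, which is not stated. Moreover, a threshold of 80% is a proportion and already scales with the number scheduled.

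Nor can it be said that the item wastes alpha. In a fixed sequence, a test that almost surely rejects passes the full level on to the next one, and the article does not give the order. The harm lies in the label and the interpretation.

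Finally, engagement with monitoring is worth reporting for a remote-care programme. That is true, and descriptive reporting keeps it.

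**Conclusion.** The point holds in a limited form. The article tests uptake of an intervention component as a key secondary efficacy endpoint. A between-arm difference would mainly reflect delivery of that component, and apart from any common data-collection readings, the article gives controls no comparable schedule for the adherence denominator. The size cannot be fixed from the documents. The power figures rest on assumed adherence rates and on 398 analysed per arm. The conclusion on interpretation needs no figure; it rests on the sections cited. The primary endpoint of death and hospitalization is not affected. The time-to-first-event wording that introduces the Section 6.2 list is a separate matter.

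**What to change.** 1. Remove adherence to home blood pressure measurement from the tested secondary efficacy endpoints, and report it descriptively at weeks 12, 56 and 84 as a process (fidelity) measure.
2. State which home readings, if any, controls are scheduled to take.
3. For any between-arm use of home readings (the adherence classification in Section 2.1 and the first MeTaRiSc item in Section 6.3), use only home readings taken on the same required schedule in both arms. An example is one identical measurement cycle at baseline and at week 84, where the schedule provides it. Leave out the additional titration-cycle readings.

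MeTaRiSc should continue to use home readings. A reader might think of substituting clinic-visit pressure, but a rule on the share of readings above a threshold cannot sensibly be applied to one or a few visit values, and the change would redefine the tertiary endpoint.

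The cost is a wording change in the protocol and analysis plan and one fewer tested secondary endpoint. No further participants are needed, and where the schedule already contains common readings, no further data are needed either.
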